### Attempts to minimize the risks associated with SVPE

All connection ports of the SVPE kit (Fig. 2), the lumens of the CVC, the blood bag, and the saline bag will be disinfected with 70% alcohol and then air-dried before sampling blood or disconnection. Strict aseptic procedures will be followed to prevent CLABSI [25–27]. The SVPE procedure will not be started or stopped temporarily after the start of SVPE in patients who develop hypotension (30 mmHg decrease in systolic blood pressure, systolic blood pressure < 90, or MAP < 65 mmHg) or cardiac arrhythmia for any reason. After correction of hypotension and/or cardiac arrhythmia, the SVPE procedure will be started or restarted if SVPE stopped due to autonomic instability. The CVC will be removed as soon as SVPE is completed or the CVC will be immediately relocated to another insertion site if a CLABSI related to the CVC used for SVPE is confirmed or strongly suspected. Patients with GBS having severe sepsis as per standardized definition (Additional file 1: Appendix 1A) due to any organ site-specific infection present on admission (except for aspiration pneumonia) will be excluded for SVPE. Otherwise, any covert infection or aspiration pneumonia, as may be indicated by leukocytosis, will be investigated and treated accordingly after consultation with a medical microbiologist. Normal hemoglobin concentration for > 18 years man and non-pregnant woman will be considered as 13 and 12 g/dL, respectively [28]. However, blood transfusion will be considered to correct severe anemia (hemoglobin level < 8 g/dL [28]) before, during, or after SVPE. Proper screening of FFP for specific infective agents (hepatitis B and C viruses, human immunodeficiency virus (HIV), and syphilis) will be performed prior to administration of FFP.

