**Fig. 3 Fig3:**
[figure not shown]
SVPE procedure for patients with GBS. A loading dose of low-molecular weight heparin (1.5 mg/kg) will be given subcutaneously at least 2 hours before initiation of SVPE; the same dose will be administered once daily or divided into two equal doses daily for 8 days or until SVPE is completed. Whole blood (7 mL/kg body weight) will be drawn from the central venous catheter into the blood transfusion bag in each session. The blood bag will be hung beside the patient for 2.5 h on a saline stand and left uninterrupted to allow plasma and blood cells to separate. The blood cells will be infused back into the patient and plasma will be discarded and replaced with fresh frozen plasma and colloid solution alternately (in equal volumes) via the closed-circuit SVPE kit illustrated in Fig. 2. In case of excessive clotting (bleeding time reduction of > 50% of baseline for that patient), aspirin (600 mg) will be administered orally at least 2 hours before the next SVPE session and continued thereafter at 150 mg orally/day until SVPE is completed. One blood bag will be used each day, with a total of six sessions/day. A total of 48 sessions will be performed over 8 days, removing approximately 8000 mL plasma in total

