### Sample size

This safety and feasibility study will enroll 20 patients with GBS for SVPE. We cannot perform a formal power calculation for this safety and feasibility study. The sample size is based on previous pilot studies in GBS [34, 35]. The baseline rate of CLABSI will be measured in parallel in patients without GBS (and not undergoing SVPE) admitted to the same study facility who require a CVC during the study period. All control patients available during the inclusion time period will be included. We expect to obtain at least 20 or more (i.e., the maximum number of patients possible during the study period) control patients without GBS who require a CVC for at least 2 days and maximum of 8 days.

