### Statistical analysis

The rate of HAIs (CLABSI, CAUTI, VAP) per 1000 device days will be calculated by dividing the number of HAIs (CLABSI, CAUTI, VAP) during the study period by the number of device days and multiplying the result by 1000. The infection safety profile for SVPE will be assessed by calculating the standardized infection ratio (SIR) to define the risk of HAI in patients with GBS treated with SVPE. The SIR will be calculated by dividing the number of observed infections by the number of infections predicted (i.e., the infection rate in the control group). The predicted HAI rate will be calculated using the rates of HAI in the control group of patients without GBS during the study period. Percentage values will be compared using chi-square test or Fisher’s exact test (two-tailed) and median values, the Mann-Whitney *U* test using SPSS 22 software (IBM Corp. Released 2013. IBM SPSS Statistics for Windows, Version 22.0. Armonk, NY: IBM Corp). Analyses will be performed on an intention-to-treat basis. All *p* values reported will be two sided, and a difference of *p* < 0.05 will be considered significant*.*

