SVPE is time-consuming, and the ability to complete uninterrupted treatment could be hampered due to autonomic dysfunction. Considering these issues, we predefined the criterion that SVPE will be considered feasible if at least 8 L of plasma can safely be removed in 8 days. Infections related to the CVC are the major safety concern during SVPE. The rate of HAI may be much higher in low-income countries, especially in the Southeast Asia, compared to high-income countries. According to the International Nosocomial Infection Control Consortium (INICC), the rates of CLABSI are significantly higher in ICUs in low-income countries (6.8 per 1000 central line-days) than the US (2.0 per 1000 central line-days) [39]. Additionally, the microbiologic spectrum varies, with a higher tendency for gram-negative bacteria to cause CLABSI in developing countries [40–43] as opposed to gram-positive bacteria in developed countries [27]. Poor infrastructure, inadequate hygienic maneuvering of vascular catheters, and a lack of knowledge regarding CVC safety may contribute to the increased risk of CLABSI in developing countries. Additionally, the indiscriminate use of broad-spectrum antibiotics further escalates multi-drug resistance.

No data is available on the prevalence of CLABSI within ICUs or HDUs in Bangladesh. Therefore, this study will systematically document the rate of CLABSI in the ICU/HDU of the institution, at which this study is being conducted, with the aim of comparing the baseline risk of infection with the risk of CLABSI associated with SVPE. Implementation of the protocol-defined safe techniques for vascular catheter handling and maintenance could improve the knowledge and awareness of the health personnel at the study facility. Eventually, a positive impact on safety is expected in terms of infection control. Though SVPE is a simple procedure, the motivation of and coordination between doctors and nurses is critical to the feasibility of this technique. Therefore, we decided to employ a questionnaire-based qualitative approach to assess the experiences of the participating medical personnel with the SVPE procedure. However, a drawback is the fact that we did not assess psychometric properties of this questionnaire in the study settings. However, our consideration is to generate some evidence within the study.

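### The standardized infection ratio is defined inconsistently: its denominator is named as a predicted count but equated with the control group's infection rate

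*Protocol article*

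**What the plan says.** The Statistical analysis section makes three linked statements.

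- It fixes the unit of the infection rate: "The rate of HAIs (CLABSI, CAUTI, VAP) per 1000 device days will be calculated by dividing the number of HAIs" by device days and scaling to 1000.
- It defines the SIR as "dividing the number of observed infections by the number of infections predicted (i.e., the infection rate in the control group").
- It then adds: "The predicted HAI rate will be calculated using the rates of HAI in the control group of patients without GBS during the study period".

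The same section presents the SIR as the way the infection safety profile of SVPE will be assessed. The article gives no total of device-days for either group, no expected count and no numerical SIR.

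Elsewhere, Secondary outcome measures lists a relative risk of CLABSI against the non-GBS controls. The primary safety outcome and the stopping rule use counts of patients with a serious adverse event.

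**The concern.** An SIR is an observed count over an expected count, so that it equals 1 when the study group has the same risk as the reference group. The expected count is the reference rate multiplied by the study group's own exposure. Here the denominator is named as a count and then explained as a rate, and the sentence that follows again speaks of a predicted rate. The multiplication by SVPE device-days appears nowhere.

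A count divided by a rate per 1000 device-days still carries units of device-time. Its value depends on how long the SVPE patients had their catheters and on the unit chosen for the rate, so it cannot be read against 1.

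The Discussion names catheter-related infection as the main safety worry with SVPE, and the control group exists to give the background risk. A literal calculation could put the ratio well below 1 when the SVPE group in fact has the higher rate.

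**Working it through.** The article states no SIR, so there is no figure to reproduce. The check compares the literal formula with the standard one.

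**Inputs**
- SVPE patients: 20 ("This safety and feasibility study will enroll 20 patients with GBS for SVPE").
- Line-days per SVPE patient: about 8. This is an assumption, from the legend of Fig. 3 ("A total of 48 sessions will be performed over 8 days") and the section on minimizing risks ("The CVC will be removed as soon as SVPE is completed").
- SVPE line-days: D = 20 × 8 = 160, with 100 to 200 (5 to 10 days each) as the range.
- Controls: 24 (Recruitment status), each with a catheter for more than 2 and up to 8 days (Patients without GBS). Taken as 3 to 8 days, this gives 24 × 3 = 72 to 24 × 8 = 192 line-days, or 24 × 5.5 = 132 in the middle.
- Illustrative CLABSI rate: 6.8 per 1000 central line-days, the external benchmark in the Discussion.

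**Formulas**, with O observed SVPE infections and r the control rate per 1000 device-days
- Expected count: E = r × D / 1000
- Correct SIR = O / E
- Literal SIR = O / r
- Literal / correct = D / 1000, whatever O and r are.

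**Size of the discrepancy (CLABSI, per-1000 unit)**

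| SVPE line-days D | Literal value at equal risk (D/1000) | Too small by (1000/D) |
|---|---|---|
| 100 | 0.10 | 10.0-fold |
| 120 | 0.12 | 8.3-fold |
| 140 | 0.14 | 7.1-fold |
| 160 | 0.16 | 6.25-fold |
| 200 | 0.20 | 5.0-fold |

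**Example at the benchmark rate.** E = 6.8 × 160 / 1000 = 1.088. With 2 observed CLABSI, the correct SIR is 2 / 1.088 = 1.84; the literal one is 2 / 6.8 = 0.29.

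**Example with an internal control rate.** Take 2 CLABSI in 160 SVPE line-days and 1 in 132 control line-days. The control rate is 1 / 132 = 7.58 per 1000 and E = 7.58 × 0.160 = 1.21. The correct SIR is 2 / 1.21 = 1.65; the literal one is 2 / 7.58 = 0.26. The apparent direction reverses.

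**Other units.** With the rate per single device-day, the literal ratio is D = 160 times too large. With the proportion of patients infected, it is 20 times too large. For CAUTI and VAP the factor is 1000 divided by urinary-catheter or ventilator days, which the article does not give.

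**How firm the control rate will be.** P(no control CLABSI) = exp(−0.0068 × control line-days):
- 72 line-days: 0.49 expected, probability 61%
- 132 line-days: 0.90 expected, probability 41%
- 192 line-days: 1.31 expected, probability 27%

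With no control event, the predicted count is zero and the CLABSI SIR has no value. In the 2/160 versus 1/132 example, the exact conditional 95% interval for the rate ratio is about 0.09 to 97. Treating the control rate as known gives 0.20 to 6.0.

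**Zero control events under the exact method.** With 2 SVPE events and none in 132 control line-days, the lower binomial limit for 2 of 2 is √0.025 = 0.158. The rate-ratio bound is (0.158 / 0.842) × (132 / 160) = 0.15, with no finite upper limit.

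**The case against.** The strongest reply is that the section does name the right denominator. The parenthesis can be taken as saying where the prediction comes from, and the next sentence says it is calculated using control rates, which suggests a further step. An analyst who knows the standard SIR would do that step, or would divide rate by rate, which gives the same answer. The rates per 1000 device days, reported alongside, would also expose an implausible ratio.

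This stands in part. A reader might infer that the planned SIR will certainly be about six times too small. The article does not support that: the figure needs a literal reading, the per-1000 unit, about 160 line-days and CLABSI as the infection. What remains is that the text offers two incompatible denominators and never writes the step that would settle which is meant.

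A reader might also infer that the safety conclusion of the trial is at risk. It is not: that conclusion rests on serious-adverse-event counts in 20 patients, and the comparison with controls is secondary. Fisher's exact test, also planned for percentages, works with no control events.

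Finally, the zero-event chances are for CLABSI alone and rest on an external rate; the Discussion says no local data exist. The article does not say whether the SIR pools infection types, and pooling would make zero control events less likely. A condensed article may also leave the choice of interval to the full protocol or analysis plan, so the lack of one is not itself an error. The exact interval below is a recommendation that accompanies the correction.

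**Conclusion.** The point holds as a contradictory definition, not as a certain miscalculation. The section equates a predicted count with a control rate and omits multiplication by SVPE device-days. Under a literal reading, the formula does not return 1 at equal risk.

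The 10- to 5-fold understatement for CLABSI is conditional on the per-1000 unit and on an assumed 100 to 200 SVPE line-days. No factor can be given for CAUTI or VAP.

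The 61% to 27% chance of no control CLABSI assumes the benchmark rate and 72 to 192 control line-days. It shows how few events the control rate may rest on; it does not show that the SIR as a whole is likely to be incalculable.

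The definition should be fixed, but because it affects a secondary measure it does not threaten the primary safety rule.

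**What to change.** Replace the SIR definition in the Statistical analysis section with wording such as:

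*For each infection type separately, predicted infections = (control infections / control device-days) × SVPE device-days, and SIR = observed SVPE infections / predicted infections. Device-days are central-line days for CLABSI, urinary-catheter days for CAUTI and ventilator days for VAP.*

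Add that the result is reported as a rate ratio with an exact conditional (binomial) 95% confidence interval. This treats both groups' counts as random. It still gives a lower bound when the controls have no events and the SVPE group has some.

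The cost is a change of wording and of the reported interval. The device-days are already needed for the planned rates, so no further data are required. The downside is a wider interval than one that takes the control rate as known.

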#### Patients without GBS

Patients ≥ 18-years of age with a diagnosis other than GBS requiring a CVC for > 2 to ≤ 8 calendar days after admission to the same ICU and HDU units in the same period of time will be eligible. Patients with healthcare-associated infection present on admission (except aspiration pneumonia) and pregnant women will be excluded from the control group.

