### Recruitment status

Recruitment has been completed with 20 cases of GBS treated with SVPE and 24 control cases without GBS in June 2017.

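### The CLABSI relative risk and the CLABSI part of the SIR depend on about 0.4 to 1.3 expected control infections, so they may be undefined and will otherwise be very imprecise

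*Protocol article*

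**What the plan says.** The Study design section says that the safety of SVPE will be set against the institution's own background risk of CLABSI, measured in a control group without GBS in the same units over the same period. Secondary outcome measures lists the relative risk of CLABSI against these controls.

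Statistical analysis defines the SIR as observed infections divided by predicted infections, and fixes the source of the prediction: "The predicted HAI rate will be calculated using the rates of HAI in the control group of patients without GBS during the study period". No other reference rate is named. The section covers CLABSI, CAUTI and VAP and does not say whether the SIR is pooled or calculated for each infection type. It also provides rates per 1000 device-days and chi-square or Fisher's exact tests on percentages.

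The size of the control group is given in three places:
- Patients without GBS: eligible controls are adults "requiring a CVC for > 2 to ≤ 8 calendar days after admission to the same ICU and HDU units".
- Sample size: "We expect to obtain at least 20 or more", with every available control taken. Here the controls are those who "require a CVC for at least 2 days and maximum of 8 days", a slightly different lower limit.
- Recruitment status: recruitment closed with "20 cases of GBS treated with SVPE and 24 control cases without GBS".

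The Discussion supplies the only rate for comparable settings, a consortium finding that "the rates of CLABSI are significantly higher in ICUs in low-income countries (6.8 per 1000 central line-days) than the US". It adds that no figures exist for Bangladeshi ICUs or HDUs.

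**The concern.** The article calls catheter infection the major safety concern with SVPE, and the comparison with controls is how the result is to be put in context. Both CLABSI ratios have the control experience as their denominator. Short catheter stays in about two dozen people give few line-days, and CLABSI is uncommon per line-day.

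Two problems follow. If no control has a CLABSI, the relative risk and the CLABSI-specific SIR have a zero denominator. If one or two do, the reference rate is set by those few patients, while an SIR by construction treats the predicted count as given. The study could therefore end without the ratio it promised on its main hazard, or with a ratio that one control infection could move several-fold. A planned randomized trial would then inherit that number.

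**Working it through.** The article gives no expected-event or precision figure for this comparison, so there is none to reproduce.

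**Inputs**
- Controls: 20 (expected minimum, Sample size) and 24 (obtained, Recruitment status).
- Catheter-days per control: more than 2 and up to 8 calendar days, taken as 3 to 8 (Patients without GBS). The mean is not stated; 5.5, the midpoint, is an assumption.
- CLABSI rate: 6.8 per 1000 line-days (Discussion). This is a cited figure, not a planning assumption.
- SVPE line-days: 20 patients × 8 days = 160, assuming the catheter stays in for the full 8 days.

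**Expected control events and chance of none**

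Expected = controls × days × 6.8/1000. P(none) = exp(−expected), Poisson.

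| Controls | Days each | Line-days | Expected CLABSI | P(none) |
|---|---|---|---|---|
| 20 | 3 | 60 | 0.41 | 66% |
| 20 | 5.5 | 110 | 0.75 | 47% |
| 20 | 8 | 160 | 1.09 | 34% |
| 24 | 3 | 72 | 0.49 | 61% |
| 24 | 5.5 | 132 | 0.90 | 41% |
| 24 | 8 | 192 | 1.31 | 27% |

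One event is expected at 1000/6.8 = 147 line-days, that is, a mean stay of 7.4 days with 20 controls or 6.1 days with 24. Below those stays the expected count is under one; above them it is not.

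**Sensitivity to the rate (5.5 days each)**
- Twice the cited rate, 13.6 per 1000: 1.5 expected with 20 controls and 1.8 with 24; P(none) 22% and 17%.
- Three times, 20.4 per 1000, 24 controls: 132 × 20.4/1000 = 2.7 expected; P(none) = exp(−2.7), about 7%.
- For P(none) to fall to 5%, the expected count must be about 3. That needs about 27 per 1000 with 20 controls (3/110) or 23 per 1000 with 24 (3/132).
- At 6.8 per 1000, the same 5% needs −ln(0.05)/0.0068 = 441 line-days: about 80 controls at 5.5 days, or 55 at 8 days.

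**Precision when the ratio exists**

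One control event in 132 line-days is 7.6 per 1000, with exact Poisson 95% CI 0.2 to 42.

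For the rate ratio, let x be SVPE events in T1 line-days and y control events in T0. Given x + y, x is binomial. Take the Clopper-Pearson limits for p and convert each with p/(1−p) × T0/T1.
- x = 2, T1 = 160, y = 1, T0 = 132: ratio (2/160)/(1/132) = 1.65. The limits for 2 of 3 are 0.094 and 0.992, which gives 0.09 to 97.
- x = 1, y = 1: 0.01 to 65.
- x = 3, y = 0: no point estimate, but a lower limit of 0.34 and no finite upper limit. The exact method still yields a usable bound.

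**The case against.** The strongest case on the other side has five parts.

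**The local rate may be higher.** The Discussion itself says that infection rates in the region may be much higher, and 6.8 per 1000 is a consortium figure. This stands in part. At three times that rate the zero-denominator problem largely goes, but imprecision remains at about 2.7 control events.

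**The SIR covers all device infections.** If it is pooled over CLABSI, CAUTI and VAP, its denominator is zero less often. This stands: the calculation applies to the CLABSI relative risk and to a CLABSI-specific SIR only.

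**Other results survive.** Device-day rates and Fisher's test can be computed with no control events, and the primary safety rule counts severe sepsis or septic shock due to CLABSI, and venous thrombosis, in SVPE patients without using controls. This stands. A reader might infer that the infection comparison would yield no result at all, or that the safety verdict is at risk. The article supports neither.

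**Zero counts and intervals belong in an analysis plan.** This stands for the choice of interval. A reader might infer that a falsely narrow SIR interval is planned, or a claim of no added risk; the article states neither. But it does fix the denominator, and that choice creates the problem.

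**It is a pilot.** The article says that no formal power calculation can be done, and it takes all available controls with no cap. That answers a demand for power. It does not answer the point that a named outcome may not be computable.

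A reader might also infer that fewer than one control infection is expected whatever the stay. That is too strong: the mean stay is not stated, and 1.1 to 1.3 are expected if all controls reach 8 days.

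**Conclusion.** The concern holds for a secondary outcome and should be addressed. On the article's own numbers of controls, permitted stays and cited rate, 0.4 to 1.3 control CLABSIs are expected, with a 27% to 66% chance of none. In that event both CLABSI ratios are undefined. Otherwise they rest on very few events, and in the worked example the interval spans about three orders of magnitude. Using the control rate as the predicted value leaves that uncertainty out of the ratio.

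The result rests on three assumptions: the 6.8 per 1000 rate carries over to this site, control stays lie between 3 and 8 days, and events follow a Poisson distribution. Counting stays of exactly 2 days, as the Sample size section would allow, lowers the expected count further. A much higher local rate would remove most of the risk of a zero denominator but not the imprecision.

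**What to change.** In Statistical analysis, make the CLABSI comparison with controls a line-day rate ratio with an exact conditional 95% interval based on both counts. Show each group's CLABSI rate per 1000 line-days with an exact Poisson interval, and label the comparison descriptive.

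State what is reported when counts are zero. With no control events, give the one-sided lower bound. With none in either group, the ratio carries no information and only the two rates with their upper limits are shown. At 6.8 per 1000 in both groups, with 160 and 132 line-days, that has probability exp(−292 × 0.0068), about 14%.

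An SIR against the cited 6.8 per 1000 may be added as a supplementary sensitivity result. It should not replace the controls, because the stated question is the institution's own background risk. It is also imprecise: 160 × 6.8/1000 = 1.09 expected, so 2 observed gives 1.8 with exact Poisson 95% CI 0.22 to 6.6, and that interval takes the external rate as known.

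The cost is analysis wording only, with no further patients or data beyond the device-days already to be counted. The downside is that the reported comparison will look less precise.
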